### Sample size calculation

We used SAS® software, V.9.4 (SAS Institute, North Carolina, USA) to estimate sample size. According to the principle of efficacy superiority design, the significance level α was set as 0.05 at two-sided. The primary efficacy endpoint of this study is the recovery rate of C-JOA at the 12th month of follow-up post operation. Assume that in severe COPLL patient population, the mean recovery rate of C-JOA in the ACAF group and the LAMP group at 12 months after operation is 63 and 51% (a mean difference of 12%), respectively, and the common standard deviation is 20%. When the two groups are randomly assigned 148 subjects in a 1:1 ratio, the statistical power can reach as high as 95%. If the subject dropout rate is 10% or less, 164 eligible subjects with severe COPLL should be randomly enrolled.

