### Statistical analysis

The study includes three analysis populations per analysis plan. For the baseline and efficacy data, we will use full analysis set (FAS), which includes all subjects who were randomized into the study groups and received the study operation scheme. According to the principle of intention to treat, subjects in FAS would be analyzed using their randomly assigned group, regardless of the actual surgical treatment received. Per-protocol population, e.g. a subset of FAS will be established further for subjects with no major protocol deviation(s), which will be reviewed and determined by the sponsor before the study database is locked. Safety set (SS) is defined to include all subjects who have received the treatment of the study-specified operation (regardless of whether they participate in the randomized assignment or not) and will be the primary analysis population for safety data. The subjects in SS will be grouped according to the actual surgical treatment received.

In this study, a two-sided *p*-value of 0.05 or less (equivalently one-sided p-value of 0.025) will be considered to indicate significance for any statistical tests, unless otherwise specified in the interim analysis section. Software R, V.4.0.4 [25] and SAS®, V.9.4 will be used for statistical analysis. Such data as demographics, baseline characteristics, surgery operation, radiographic data and safety will be summarized according to treatment group.

The primary endpoint of this study is the C-JOA recovery rate at 12 months post operation. It will be analyzed with the use of analysis of covariance (ANCOVA), with random stratification factors (if appropriate) and the treatment group as fixed factors, and the baseline level of C-JOA score as covariate. The least squares mean (LSM), the difference from the control group and the confidence interval (CI) of each treatment group will also provided for statistical analysis.

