In addition, a mixed model repeated measures (MMRM) will be used as supportive analysis when appropriate. MMRM analysis includes treatment group, time and time treatment group interaction as fixed effects, baseline level as covariate, and patients as random effects. When there are missing data, multiple imputation method will be applied as the primary analysis; those results from the last observation carry forward method (LOCF) and the as-observed data analysis will play roles as sensitivity analyses. If the data distribution does not meet the statistical hypothesis of ANCOVA, a set of rank-based analysis will be the primary one. The LSM, the difference from the control group and the CI of each treatment group will be also provided for statistical analysis. For MMRM and ANCOVA, the two-sided *p*-values will be provided when compared with the control group.

To investigate the consistency of the trial conclusions among different subpopulations, the subgroup analysis with regards to the primary efficacy endpoint will include but not limited to the following baseline factors: gender; age group; duration of complaining symptoms; diabetes status; smoking status; count of vertebrae segments involved; type of COPLL; K-line status; occupation ratio; C-JOA score; Nurick grade and status of hypersignal of spinal cord. The occupation ratio (OR) is defined as the biggest ratio of COPLL thickness to anteroposterior diameter of the bony spinal canal on the axial computed tomography image. A forest plot will be also provided as a useful display of estimated treatment effects across subgroups.

For VAS pain score and NDI index as continuous variables, the analysis method of between-group comparison is similar to those used for the primary endpoint. For cervical Nurick grades as an ordinal variable, the common odds ratio will be estimated by using ordinal logistic regression analysis (proportional odds model) to reflect the shift of full distribution of each grade between the two groups 12 months after operation. The adjusted and unadjusted common odds ratio and its 95% CIs will be calculated. When using the model to adjust prognostic factors, the important prognostic factors mainly include random stratification factor as appropriate, gender, age and baseline Nurick score, which will be clearly specified in the statistical analysis plan before the database lock.

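### The primary test depends on the observed outcome distribution: if the rank-based switch fires, it no longer tests the mean difference the trial is sized for

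*Protocol article*

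**What the plan says.** All references are to the Protocol article.

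- **Statistical analysis, primary endpoint.** "The primary endpoint of this study is the C-JOA recovery rate at 12 months post operation". On the method: "It will be analyzed with the use of analysis of covariance (ANCOVA), with random stratification factors (if appropriate) and the treatment group as fixed factors", with baseline C-JOA as covariate.
- **Statistical analysis, next paragraph.** "If the data distribution does not meet the statistical hypothesis of ANCOVA, a set of rank-based analysis will be the primary one". Here the statistical hypothesis of ANCOVA can only mean its distributional assumptions.
- **Same paragraph, reporting.** "The LSM, the difference from the control group and the CI of each treatment group will be also provided for statistical analysis". On p-values: "For MMRM and ANCOVA, the two-sided *p*-values will be provided when compared with the control group". Neither sentence mentions the rank-based route.
- **Sample size calculation.** Mean recovery rates of 63% and 51% are assumed, a difference of 12 points, and "the common standard deviation is 20" percent. With 148 subjects at 1:1 and two-sided alpha of 0.05, the stated power is 95%. Enrolment is 164 to allow for 10% dropout.

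**The concern.** The distribution of the 12-month recovery rate is known only once outcome data exist. The rule therefore leaves open, until then, which analysis decides the trial. The two candidates are not two ways of testing one thing. ANCOVA tests a difference in adjusted means. A rank-based test asks whether values in one arm tend to be higher than in the other. When the arms differ in shape, one can be null and the other not.

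Three things are at stake:

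1. The sample size is justified for a mean difference, so after a switch the primary test is not the one that was powered.
2. The effect estimates promised are on the mean scale, so a primary p-value from ranks would stand beside an interval that answers a different question and may not agree with it.
3. A confirmatory trial should have one primary hypothesis fixed before outcomes are examined.

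The endpoint makes a departure from normality conceivable. By the formula under Primary efficacy outcome, the recovery rate cannot exceed 100%, has no matching lower limit, and is divided by 17 minus baseline, so its spread grows as baseline approaches 17.

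**Working it through.** **1. The plan's own figure.** Inputs from Sample size calculation: difference 12, SD 20, two-sided alpha 0.05, power 95%, 1:1.

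Normal approximation: n per arm = 2 × (1.960 + 1.645)² × 20² / 12² = 2 × 13.0 × 2.778 ≈ 72.2, so 73 per arm. With the noncentral t distribution, 73 per arm gives 94.96% and 74 per arm gives 95.2%, so 148 is the smallest equal-arm total reaching 95%. Dropout: 148 / 0.90 = 164.4, and 164 × 0.90 = 147.6, in line with the stated 164. The figures reproduce, and they are built wholly on a difference in means.

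**2. Does the switch, applied as a fixed rule, inflate type I error?** The article gives no trigger, rank method or baseline distribution, so all of these are assumptions:

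- trigger: Shapiro-Wilk test on ANCOVA residuals at 0.05;
- fallback: rank ANCOVA;
- 74 per arm, integer C-JOA;
- post = pre + (17 − pre) × N(51, 17)/100 + N(0, 1), rounded and limited to 0–17, with no treatment effect.

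| Assumed baseline mean / SD | Resulting SD of recovery rate | Switch fires | Type I error, ANCOVA alone | Type I error, switch rule |
|---|---|---|---|---|
| 9 / 2.5 | about 23 | about 28% | 4.2% | 4.3% |
| 10 / 3 | about 28 | about 81% | 5.4% | 6.0% |
| 12 / 2.5 | about 36 | about 99% | 4.7% | 4.7% |

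Repeat runs of the switch rule stayed within 4.3% to 6.0%. In this model ANCOVA and rank ANCOVA gave the same verdict in 97% to 98% of null trials.

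A second model drew the recovery rate directly with SD 20. With a near-normal shape (baseline 10 / 2.5) the switch fired in about 10% of trials and the rule's error was 5.3%. With a deliberately skewed shape (baseline 11 / 2.5) it fired in every trial and the error was 5.1%.

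**3. Does the switch change the hypothesis?** Take 74 per arm with equal means of 57 and SD 20, one arm normal and the other skewed towards low values. These shapes are invented for illustration. The t test rejected in 4.8% of trials, Mann-Whitney in 13.1%, and the switch rule in 12.8%. The excess is not a false positive for the hypothesis that Mann-Whitney tests. It shows that the rule has moved to another hypothesis, while the sample size and the promised estimates stay with the mean.

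**4. What would keeping ANCOVA cost?** With a 12-point effect, rank ANCOVA had about 1 to 2 points more power than ANCOVA in the first row of the table, and 10 to 12 points more in the other two. In the second model, ANCOVA had 93.0% against 92.2% for rank ANCOVA with near-normal data, and 93.9% against 99.2% with skewed data.

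**The case against.** The strongest case against is that the article states a rule, not a free choice, and the rule is nearly harmless for type I error. That stands. A reader might infer substantial alpha inflation, but step 2 does not show it. Error rates of 5.2% to 7.3% arise only if the analyst may take whichever of ANCOVA and rank ANCOVA is significant, and the article does not permit that.

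A reader might also infer that the switch is likely to fire. The article does not support this. The high firing rates come from assumed baselines that give SDs of about 28 and 36, well above the stated 20. Neither the baseline distribution nor the trigger is given.

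A third tempting reading is that a set of rank-based analyses means several competing primary p-values. The same idiom is used under Primary efficacy outcome for one set of C-JOA scores per visit, and the sentence goes on in the singular. Several tests cannot be inferred with confidence.

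Nor does the open-label design show that results by arm will be seen before the method is chosen. The check could be made on pooled or blinded data.

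Finally, the name of the rank test, the diagnostic and its threshold are details that an article may leave to the analysis plan, and their absence is not the point here. But this defence does not reach the core. However fully the switch were specified, the primary hypothesis would still be settled by the outcome data. A blinded check would limit selection but would not restore the match between the test, the effect estimate and the sample size.

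**Conclusion.** The concern holds as a matter of which hypothesis is primary, and it should be fixed. The article states both the conditional replacement and the mean-based sample size and estimates, and they are compatible only if the switch does not fire. This conclusion rests on the text and needs no simulation.

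The size is moderate. Type I error under a fixed trigger and one fixed rank test is about 4% to 6%, given the assumed baselines, trigger and fallback. The firing rate is unknown: about 10% to 99% across assumed scenarios, and about 28% in the tabulated scenario nearest the stated SD. The sample size calculation is sound and is not in question.

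**What to change.** Delete the sentence that makes a rank-based analysis primary. State that ANCOVA on the mean recovery rate, with the covariates and missing-data method already planned, is the single primary analysis whatever the distribution. Name one rank-based analysis, such as rank ANCOVA with the same covariates, as a sensitivity analysis that cannot replace the primary result.

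Heteroscedasticity-robust standard errors (for example HC3) are an option if unequal variance is a worry. They are not required, because ordinary ANCOVA held its error rate in the simulations.

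The change is to wording only. The 148 evaluable and 164 enrolled subjects stand, since they are already based on means. The price is the power forgone against a rank test when tails are heavy, as set out in step 4 of the working. If the sponsor thinks that loss too great, the alternative is to name one rank-based analysis as primary from the outset, with its own effect measure, a way to combine it with multiple imputation, and a sample size justified for it.

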### Interim analysis

Two formal interim analyses of efficacy data are planned when one-third and two-thirds of the enrolled subjects have completed at least 12 months of follow-up, respectively. The treatment efficacy and the occurrence of adverse events will be then reviewed by an independent Data and Safety Monitoring Board (DSMB), when the sample size might be also re-estimated and adjusted based on accumulative data of primary efficacy endpoint as necessary (Cui L et al., 1999) [27].

In the interim analysis of efficacy, the Haybitt-Peto boundary will be used (Haybitt 1971 [28]; Peto et al. 1976 [29]) to control the overall type I error. The alpha boundary is to be consumed at 0.0001 (one-sided and nominal level) at each interim analysis. The boundary value at the final stage will be kept at 0.025 at one-sided after the two scheduled interim analyses or be derived to maintain the Type I and Type II error probability levels if any ad hoc interim analysis is added.

### Study committees

Four committees are planned in the whole study. A Steering Committee was well organized to oversee the governance of the study. From independent external oversight, a DSMB was established and chaired by a surgical expert and also included another DSMB statistician and one radiologist as well. The members of the DSMB serve in an individual capacity and provide their expertise and recommendations on a timely basis to the study Steering Committee.

A Technical Training Committee (TTC) was organized to develop a training manual on ACAF technique, carry out field lecture at each branch centre and perform demo surgery as appropriate. Besides, all of the radiographic scans (X-ray, CT and magnetic resonance imaging [MRI]) in the study will be forwarded to an independent Radiographic review Committee (IRC) for retrospective review on a regular basis.

## Discussion

In the three recent exploratory studies [13, 14, 16], the pilot use of ACAF technique (or called vertebral body sliding osteotomy [VBSO] in principle) showed promising treatment benefits in COPLL patients. The novel surgery technique can achieve anterior direct decompression without separating and removing ossification. Its basic principle is to expand the spinal canal by anteriorly translating the involved vertebral bodies with any ossified masses [15, 16] (Fig. 2). Based on surgeons’ preference, this novel technique was initially proposed more suitable for severe COPPL patients as opposed to continue conventional anterior or posterior approaches for non-severe patients. Patients included in the small-sized studies are those with OPLL involved three or more vertebrae and a canal occupying ratio of more than 60% [13], or those with at least three levels of cervical compression caused by OPLL [14], or those with negative K-line and a large OPLL mass or kyphotic cervical alignment [16]. In line with these findings, we designed this new study to have a statistical hypothesis enriched in the severe COPLL subpopulation. To make a balanced assignment of ACAF versus LAMP across each stratum of patients and validity of subsequent statistical comparison, therefore, we pre-specified several stratification factors when conducting randomized assignment of the two treatments among enrolled subjects. This had better help set up any statistical modeling in the data analysis.

The use of anterior controllable antedisplacement and fusion belongs to one of anterior approaches, which are usually high technically demanding. However, the excellent neurologic outcome noted in the severe COPPL patients might be extended to the whole COPPL population as long as the spine surgeons in the study are rich in spine surgery experience and can also follow a standardized operation schema after uniform training held by TTC. This is why our study operation team in the sponsor’s site will design a training manual of ACAF technique, carry out field lecture and perform surgery in concert for the first several cases of each site. On the other hand, the study site is included as one of randomization factors, which provides a data basis for analyzing potential site effect in the future.

Furthermore, for purpose of better data quality, the study team will employ a dedicated clinical monitor team for source data verification. The radiographic data will be centrally reviewed by the IRC. Due to the limited OPLL patients at some of our study sites, it may take a long time to recruit the sample size required for this study. Moreover, we face the challenge of subjects’ follow-up issue to collect primary efficacy data especially in the long run. We will also utilize additional patient accrual and follow-up services from a dedicated third-party clinical research coordinator team. An electronic data capture system with audit trails will also be used in the study.

Based on this adequate and well-controlled study, we expect to obtain solid study data and with them to demonstrate whether this novel ACAF technique is more favorable than LAMP in the selected study population. We have a plan to formulate an expert consensus with our study findings and also develop a COPLL-specific clinical practice guideline as appropriate. All of these after publication will be shared with participating hospitals and the academic communities to promote the clinical management of severe COPLL patients.

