## Methods and design

### Study design

The STAR study (ClinicalTrials.gov number, NCT04968028) is a multicentre, randomized, open-label, parallel-group, active controlled trial that aims to demonstrate more favorable clinical benefits of ACAF as compared to conventional LAMP in severe COPLL patients. It will be conducted following the Consolidated Standards of Reporting Trials (CONSORT) statement (http://www.consort-statement.org/). Approximately twelve clinical centres in China will participate in this study. A brief flowchart of this study is provided in Fig. 1.

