### Description of the interventions

The enrolled subjects will be randomized to undergo the novel ACAF or conventional LAMP surgery. In order to minimize the potential bias of the trial data, all patients would be operated on by senior spine surgeons from spine surgery team at each site who are highly experienced in performing the two trial interventions. All patients in the study will accept the same surgical devices. All the consumables used in the operation are from the same manufacturer, and the operations will be carried out in strict accordance with the unified standard.

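### The Methods rely on site surgeons already highly experienced in both operations, but the Discussion has the sponsor's team operating jointly on each site's first cases; the article must say whether these are randomised patients

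*Protocol article*

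**What the plan says.** The protocol article describes the operators in three places.

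- **Description of the interventions.** To limit bias, all patients are to be treated by "senior spine surgeons from spine surgery team at each site who are highly experienced in performing the two trial interventions". The same paragraph adds common devices and a unified operating standard for both arms.
- **Study committees.** A Technical Training Committee is to "develop a training manual on ACAF technique, carry out field lecture at each branch centre and perform demo surgery as appropriate".
- **Discussion.** The good results in severe disease are expected to extend provided that the surgeons have ample general spine experience and keep to a standard procedure once they have been trained. To that end, "our study operation team in the sponsor’s site will design a training manual of ACAF technique", and will also "carry out field lecture and perform surgery in concert for the first several cases of each site".

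No training or joint operating is described for LAMP. The Statistical analysis section defines the safety set as everyone who received the study operation, whether or not they were randomised, grouped by the surgery actually received. The Study design section states: "Approximately twelve clinical centres in China will participate in this study".

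**The concern.** The first statement offers existing expertise in both operations as the protection against operator bias. The other two describe sites that are taught ACAF and helped through their first cases by a team from the sponsor's site. Surgeons already highly experienced in ACAF at every site would not obviously need that help.

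If the helped cases are trial patients, the arms differ early on in who operates as well as in which operation is done. The estimated difference would then mix three things: the technique, the presence of the sponsor's team (which may favour ACAF) and the learning curve (which may count against it). Site is a minimisation factor, but that does not separate joint from independent cases within a site.

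If the helped cases are not trial patients, the efficacy comparison is untouched. The safety set as worded could still include them, and they would all be ACAF.

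**Working it through.** **The plan's own figure.** With 74 per arm, a difference of 12 points, SD 20 and two-sided alpha 0.05, power is 95.4% by normal approximation and 95.2% by noncentral t. The stated 95% reproduces. For dropout, 148/0.9 = 164.4, against 164 stated. Nothing in this point changes the sample size.

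**Inputs.** 164 randomised 1:1, so 82 per arm (Sample size calculation); about 12 centres (Study design). The number of joint cases per site, k, is not given; k = 2 to 4 is my assumption. Equal accrual across sites is also assumed.

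**Patients per site.** 164/12 = 13.7, of whom 82/12 = 6.8 are ACAF.

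**Share of the ACAF arm operated on jointly**

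| Reading | k = 2 | k = 3 | k = 4 |
|---|---|---|---|
| Joint cases are not randomised | 0% | 0% | 0% |
| Randomised; k counts ACAF cases: 12k/82 | 24/82 = 29% | 36/82 = 44% | 48/82 = 59% |
| Randomised; k counts cases of both arms: (12k/2)/82 | 12/82 = 15% | 18/82 = 22% | 24/82 = 29% |

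**First interim.** One-third of 164 is about 55 patients, or 27.3 per arm, which averages 27.3/12 = 2.3 ACAF patients per site. Stopping uses one-sided 0.0001 (Interim analysis), z = 3.72. The standard error is 20 × √(2/27.3) = 5.41, so the boundary is an observed difference of 3.72 × 5.41 = 20.1 points. Under the planned 12 points the chance of crossing is Φ((12 − 20.1)/5.41) = Φ(−1.50), about 7%.

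**Cost of a sensitivity analysis that excludes both arms' early patients.** With k ACAF cases per site and as many LAMP patients randomised in the same period, 2k × 12 patients are excluded.

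- k = 2: 48 excluded and 116 left; after 10% dropout 52.2 per arm; power for 12 points about 87%.
- k = 4: 96 excluded and 68 left; after 10% dropout 30.6 per arm; power about 65%.

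If k counts both arms' cases, half as many are excluded (24 to 48), and power is about 92% to 87%.

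**The case against.** The strongest reply is that the article never says the joint cases are randomised. The Study committees section speaks of demonstration surgery at the centres, and the safety set definition contemplates operated subjects outside the randomisation, so these may be run-in cases. This stands, and it is why zero belongs in the range.

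A second reply is that the conflict is mild. Operating in concert means that site surgeons take part, they may count as experienced once trained, and a unified standard covers both arms. Teaching the new technique but not the conventional one is natural in such a comparison. This softens the conflict but does not remove it: the Methods state the experience as a fact about all patients, while the Discussion makes general spine experience plus training the condition.

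Third, equal accrual is doubtful, since the Discussion expects few patients at some sites. High-volume sites would have a smaller joint share and low-volume sites a larger one. The percentages are therefore indications only.

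Fourth, the analysis plan and full protocol are not shown and may already contain a suitable sensitivity analysis. That is fair, so its absence from the article is not counted as a fault. The conflict between the sections remains.

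A reader might also infer that the first interim would rest almost wholly on joint cases and could stop the trial on them. The document does not support this. About half of the interim patients are LAMP, for which no joint operating is described, and stopping needs roughly a 20-point observed difference. What remains is the ACAF arm's contribution to a possible sample-size re-estimation.

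**Conclusion.** The inconsistency is real and should be resolved. Its effect depends on a fact that the article does not state.

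- **Joint cases not randomised:** no effect on the ACAF arm of the efficacy comparison, but the safety set could admit ACAF-only training cases with no LAMP counterpart.
- **Joint cases randomised:** 29–59% of the ACAF arm if only ACAF cases count, or 15–29% if both arms' cases count. This rests on 2 to 4 cases per site, 12 sites and equal accrual, the first and last of which are assumptions.

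The net direction of any bias cannot be determined. It would be tempting to conclude that much of the ACAF arm does not test the technique as claimed. The document does not support that, because neither the randomised status nor the number of these cases is given. No error is shown in the primary test or the sample size.

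**What to change.** 1. Reconcile the Description of the interventions, Study committees and Discussion sections. State whether the jointly operated cases are randomised trial patients, how many are planned per site, and whether cases of one or both arms are counted.
2. Limit the between-group safety comparison to randomised patients and report any training cases separately. This narrows the present safety set definition for that comparison, and the text should say so.
3. If joint cases are randomised, record for each patient whether the operation was joint and, for ACAF, the case number at the site.
4. In that case also pre-specify a supportive sensitivity analysis of the primary endpoint that excludes patients of both arms randomised at a site before its joint-surgery period ended. A treatment-by-period estimate would serve equally. Excluding by date in both arms keeps the comparison randomised; dropping only the joint ACAF cases would not.

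The primary intention-to-treat analysis stays as it is. I would not ask for this split at the first interim: with about 2.3 ACAF patients per site there may be almost no post-training cases to compare.

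The cost is some wording, two case report form fields and one analysis. That analysis could lose about 48 to 96 of 164 patients, with power falling to about 87% to 65%, so it can only be supportive.
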